Similar concerns are related to frequent ED visits. Frequent ED visitors are commonly defined as people having 4 or more ED visits during the past 12 months [18], and they are more likely to suffer from chronic somatic diseases, drug and alcohol abuse and acute mental illness [18]. Predictors for recurrent ED visits due to acute mental health problems are usually substance abuse, single status and homelessness [19].

In addition to readmission rates and frequency of ED visits, length of stay (LOS) is another important quality of care indicator. LOS is defined as the number of days between admission and discharge dates for each admission experienced [20]. LOS is likely to be multifactorial, but some factors associated with longer LOS have been consistently identified: biological sex (being male), ethnicity (being Asian, Black, or having mixed background), accommodation status (being homeless) and having the primary diagnosis of psychosis. Although there is no ideal LOS, current international recommendations advocate for an early discharge as soon as stabilization is successful, with continuation of treatment in less restrictive environments [20]. On the contrary, concerns about prioritizing shorter stay admissions include increasing medical negligence and favouring the revolving door cycle, which can be aggravated with a history of repeated admission and frequent ED visits [20, 21].

Besides the high rates of health services utilization, mental disorders are associated with major social and economic consequences for patients and their families. Patients with mental disorders have high mortality rates [22], poor quality of life [23], lower self-esteem [24], and lack of educational and income-generating opportunities, thus limiting their chances of economic independence and depriving them of social networks and status within the community [14]. Individuals with mental disorders also experience a variety of chronic physical health problems, such as hypertension and cerebrovascular diseases [15]. Despite the pervasive need for mental health treatment among individuals with mental disorders, it is generally acknowledged that many do not use healthcare services [25].

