The study seeks to address the following research questions:A.Effectiveness and Impact on Health Services Utilization of the RASP:Did RASP increase the volume of patients referred by PHP? Measured by the number of patients referred by a PHP for a psychiatrist consultation before and after RASP implementation.Did RASP increase the proportion of patients triaged by Central Intake services who had direct access to psychiatric consultations? Measured by the proportion of referrals received by central intake that were booked directly for psychiatry consultation, before and after RASP implementation.Did RASP reduce wait times for access to psychiatrists in the publicly funded MHAP? Measured by the number in calendar days waiting from date referral was received by Central Intake to date patient is scheduled for a psychiatric consultation before and after RASP implementation.Did RASP improve efficiency of the Community Mental Health Programs (CMHP) to address the mental health needs of patients with complex mental health needs? Measured by wait-times for assess to psychiatrists within the CMHP following a referral by a mental health clinician before and after RASP implementation.Did RASP reduce the volume of patients referred by PHP to the ED for a psychiatric consultation? Measured by the number of patients referred by a PHP for a psychiatrist consultation at the ED before and after RASP implementation.Did RASP reduce ED visits, mobile crisis visits, and inpatient mental health services utilization? Measured by the number of mental health and addictions (MHA)-specific ED visits, number of mobile crisis visits, number of MHA-specific hospital admissions, and number in calendar days in LOS for Central Zone patients, before and after RASP implementation.Did patients who attended the RASP and opted to participate in the Text4Support RCT differ in their health services utilization compared to patients who opted not to participate in the Text4Support RCT? Measured by the number of MHA-specific ED visits, number of mobile crises calls, number of MHA-specific hospital admissions, and LOS in calendar days, one-year post-RASP assessment.What are the costs and benefits to Nova Scotia Health from having a RASP for mental health? Measured by the net cost savings associated with RASP considering costs associated with the program and costs saved from avoided high-cost health services utilization (ED visits, mobile crisis visits, and inpatient treatments).B.Perspectives and Experiences of Healthcare Partners and PatientsWhat are healthcare partners' perceptions related to the impact of the RASP on access to community mental health care for patients and support for primary care providers? Measured by qualitative data from key informant interviews with program directors, psychiatrists, primary healthcare providers, MHA service leaders, and representatives from community organizations.What are the patients' perceptions related to their overall experience and satisfaction with the service received? Measured by quantitative and qualitative data from the RASP's satisfaction survey and qualitative data from focus group sessions with a sub-group of the assisted population.C.Population Characteristics and Mental Health MeasuresWhat proportion of patients seen at the RASP continued their treatment with PHP? Measured by the number of patients fully discharged back into the care of their primary healthcare provider with treatment recommendations (chart review data).What proportion of patients seen at the RASP were referred to a community mental health program? Measured by the number of patients referred to a community mental health program by RASP psychiatrists (chart review data).What proportion of patients seen at RASP needed additional psychiatric evaluation at the RASP? Measured by the number of re-referrals to RASP by a PHP.What are the sociodemographic characteristics of the assisted population at program entry? Measured by the frequency and percentages of the sociodemographic characteristics (e.g. age, sex of birth, gender, ethnicity, employment status, source of income, income range, relationship status, family support, housing status, education, provincial zone) (chart review data).What is the status of patients’ recovery and health quality index, and the prevalence of likely major depressive disorder (MDD), likely generalized anxiety disorder (GAD), low resilience, childhood trauma, substance use, and suicide risk at program entry? Measured by patient-completed validated scales scores (chart review data).What is the prevalence of patients' diagnoses made by RASP psychiatrists at program entry? Measured by the frequency and percentages of each psychiatry diagnosis after psychiatry assessment (chart review data).What are the risk factors for ED presentation for mental health concerns and inpatient psychiatric treatments? Measured by Odds Ratios using logistic regression models with sociodemographic and clinical data from the assisted population one year before and after RASP assessment date.

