
### Hypothesis

Based on the project Logic Model (Fig. 2), we anticipate that the RASP initiative will yield positive impacts in the short, medium, and long terms, leading to substantial changes in the capacity of mental health support and primary health care providers. Specifically, we hypothesize that RASP will result in a minimum 10% reduction in high-cost health services utilization (e.g. ED visits, mobile crisis visits, and inpatient treatments) and corresponding 10% cost savings. Additionally, we anticipate a reduction in the wait times for patient consultations with psychiatrists within the publicly funded MHAP to less than 30 calendar days. This forecast is expected to be found in both within-subject and between-subject comparisons. In addition, we hypothesize that at least 90% of patients attending the RASP will express satisfaction with the services received. Finally, we hypothesize that primary care providers and healthcare partners will express high satisfaction with RASP. These hypotheses are derived from anecdotal evidence gathered from a similar program implemented at Fort McMurray between 2013 and 2016 by the Senior Investigator.

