### Outcome measures

Primary outcome measures will include the mean differences in the frequency/duration/related costs of high-cost mental health services utilization (i.e., volume and proportion of mobile crisis visits, ED visits, hospital admissions and readmissions and associated LOS for each admission) between one year pre- and post-assessment date for same patients at RASP (within-subject comparison) and between the IG (RASP) and CG (historical data) (between-subjects comparison). Other primary outcome measures will be the mean difference in the number and proportion of total referrals booked directly for a psychiatrist and the number of calendar days for access to psychiatrists, also compared to the control group.

Secondary outcome measures include the mean difference in the frequency/duration/related costs of high-cost health services utilization one year post for patients who access the RASP and participate in the Text4Support RCT (to receive either daily supportive text messages or a single text message with a link to e-mental health resources) and patients accessing RASP but who do not participate in the Text4Support RCT. Other secondary outcome measures include a descriptive summary of the sociodemographic and clinical characteristics of the assisted population, the mean scores on the Patient Health Questionnaire 9 (PHQ-9) [38], Generalized Anxiety Disorder 7 (GAD-7) [39], World Health Organization 5 (WHO 5 Well-Being Index) [40], Brief Resilience Scale (BRS) [41], Recovery Assessment Scale (RAS) [42], Adverse Childhood Experience (ACE questionnaire) [43], Brief Substance use Craving Scale (BSCS) [44], and the Columbia-suicide severity rating scale (C-SSRS) [45], as well as the prevalence of likely MDD, GAD and low resilience. Patient overall impressions (i.e. barriers to accessing RASP, satisfaction level, likely recommend the service to others, etc.) and impressions on the experience (i.e. feelings of welcomeness, respect, enough time to talk, the problem addressed, and understanding of treatment) are part of the patient satisfaction quantitative evaluation. An in-depth evaluation of healthcare partner impressions and patient satisfaction will be obtained through qualitative key informant interviews until saturation is reached and no new themes and subthemes emerge.

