### Data analysis

#### Quantitative analysis

Quantitative data will be analyzed using descriptive and inferential statistics by using SPSS version 26 for Windows [46]. First, we will summarize the study participants' sociodemographic and clinical descriptive characteristics. Primary outcomes comparing the pre-and post-enrollment health services utilization for patients accessing RASP will be analyzed using descriptive and inferential statistical analysis, including Chi-Square and independent sample t-tests. For the primary outcome involving control populations, pre- and post-enrollment health services utilization variables will initially be compared using an analysis of covariance (ANCOVA) with the intervention condition (attended RASP) as the independent variable, the relevant health services utilization data one year pre attendance of appointment with RASP psychiatrist or community mental clinician as the covariate, and the relevant high-cost health services utilization data one year post attendance of appointment with a RASP psychiatrist or attendance with mental health clinicians in the community mental health program as the dependent variable. In each case, checks would be conducted to ensure no violation of regression slopes and reliable measurement of the covariate. We will perform sensitivity analyses of covariance to explore the impact of the imputation of data loss at each time point on health services utilization. In addition, we will perform propensity score matching and regression analyses adjusting for the periods pre-, during and post COVID-19 pandemic in order to strengthen the comparability of the groups and enhance the validity of the study's findings.

We will also use an ANCOVA to compare high-cost health services utilization data for one-year pre- and post-RASP attendance for the subset of patients who attend RASP and either participate or do not participate in the Text4Support RCT. For this analysis, the intervention condition (participants in the Text4Support RCT) will be the independent variable, the relevant health services utilization data one-year pre-attendance of appointment with RASP psychiatrist will be the covariate, and the relevant high-cost health services utilization data one-year post attendance of appointment with a RASP psychiatrist will be the dependent variable.

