#### Health economic evaluation

We will conduct an economic evaluation through an effectiveness-implementation science lens. Specifically, we will conduct a cost-consequence analysis (CCA) from a Canadian single-payer perspective. The CCA will involve a disaggregated comparison of the costs and benefits (consequences) associated with RASP. The disaggregated analysis reports the intervention effects for the relevant primary and secondary outcomes in their natural units to aid value for money assessments. The study design, population, setting, and location are described elsewhere in this proposal.

We will compare outcomes (ED visits, crisis calls and inpatient days) and costs in the intervention group to the control group. Costing includes costs associated with the pre-implementation, implementation, and ongoing costs. These costs will include space and utilities, new hires specific to RASP, supplies, materials, and equipment, travel costs, volunteer time, and other in-kind donations. We will exclude all research-related costs. These cost data will come from the project documents. In addition, we will collect cost data on health resource use from the case costing centre in the Nova Scotia Health, supplemented with data from the literature if necessary.

Costing will also include costs saved from avoided ED visits, crisis response services and inpatient treatments. Cost analyses will use Nova Scotia Health 2023 costs to ensure relevance to decision-makers. We will estimate the intervention effect for the outcomes using appropriate treatment-effect econometric models with bootstrapping to quantify the uncertainty around the estimates. To enable cost comparisons, the cost of the current models of community-based mental health services, which involve waitlisting of all non-urgent patients (regardless of referral source and reason for referral) to see a mental health clinician as a gateway to receipt of community mental health services, including psychiatry, will be compared with the costs of alternative treatments offered expeditiously through RASP and primary care and community providers. We will compute the net cost savings associated with RASP. Our economic analysis will follow guidelines for economic evaluations, including using probabilistic sensitivity analysis to quantify the uncertainty around the implementation costs [48].

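### Read as worded, the primary length-of-stay outcome exists only for admitted patients, so it can move in the opposite direction to total inpatient days

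*Protocol article*

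**What the plan says.** Methods, Outcome measures, sets the primary outcome as "mean differences in the frequency/duration/related costs of high-cost mental health services utilization". The components listed after that end with "hospital admissions and readmissions and associated LOS for each admission". Two contrasts are intended: RASP patients against themselves in the preceding year, and RASP patients against the historical control group.

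LOS is defined once, in the Background section on mental health burden: "LOS is defined as the number of days between admission and discharge dates for each admission experienced". The research question on utilization (Methods, Study objectives) asks for "number of MHA-specific hospital admissions, and number in calendar days in LOS for Central Zone patients", without saying whether the days belong to a stay or to a patient. The Health economic evaluation will compare "outcomes (ED visits, crisis calls and inpatient days) and costs in the intervention group to the control group".

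For the between-group contrast, Quantitative analysis plans an ANCOVA. The post-year value is the dependent variable, with "the relevant health services utilization data one year pre attendance of appointment with RASP psychiatrist or community mental clinician as the covariate". For the pre/post contrast it names Chi-square and independent-sample t-tests.

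Nowhere does the article say that days are summed per patient over the year, or that a patient without an admission counts as 0.

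**The concern.** A length of stay exists only if there is a stay. Fewer inpatient treatments are a stated aim of RASP, and admissions are themselves a primary outcome. A mean of LOS over admissions therefore compares sets of stays that the programme may itself have selected. Propensity matching and adjustment for baseline variables or pandemic period do not remove selection that arises after the intervention.

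At stake is how the inpatient-duration component is read against the hypothesis that "RASP will result in a minimum 10% reduction in high-cost health services utilization". A higher mean LOS could accompany a real fall in inpatient use, and a lower one need not show how much inpatient use has fallen. The primary LOS result and the economic result on inpatient days could then point in opposite directions, and the article has no rule for reconciling them.

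**Working it through.** **What there is to reproduce.** The article gives no figure for LOS. Its sample-size calculation concerns an aggregated utilization mean. The admission rate, the LOS distribution and the kind of stay that RASP might avert are not given, so every input below is an assumption except the expected 2,500 patients per group.

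**Direction, in general.** Let N admissions have mean length m, and let k of them, with mean length s, be averted.

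- Total bed-days change from Nm to Nm − ks, so they always fall.
- Mean LOS changes from m to (Nm − ks)/(N − k), a change of k(m − s)/(N − k).
- The mean therefore rises if s < m, is unchanged if s = m, and falls if s > m.

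**Illustration.** Assume 100 admissions, 50 of 5 days and 50 of 25 days, with 20 averted.

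- Before: 50×5 + 50×25 = 1,500 bed-days; 1,500/100 = 15.0 days.
- Averting 20 short stays: 1,500 − 20×5 = 1,400 bed-days (−6.7%); 1,400/80 = 17.5 days (+16.7%).
- Averting 10 short and 10 long: 1,500 − 50 − 250 = 1,200 bed-days (−20%); 1,200/80 = 15.0 days (no change).
- Averting 20 long stays: 1,500 − 20×25 = 1,000 bed-days (−33.3%); 1,000/80 = 12.5 days (−16.7%).

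Admissions fall by 20% in all three cases and bed-days always fall, yet mean LOS goes up, stays level or goes down.

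**Range.** Four assumed mixes were tried: 3 and 21 days (50% short), 5 and 30 (40% short), 3 and 14 (60% short), 7 and 28 (30% short). With 10% to 30% of all admissions averted, all of them short, mean LOS rises by 6.6% to 32.1% and bed-days fall by 2.5% to 12.2%. These percentages do not depend on the admission rate.

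**The per-patient total.** Take 2,500 patients and assume 8% are admitted once (200 admissions), half for 3 days and half for 21.

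- Before: 100×3 + 100×21 = 2,400 bed-days; 2,400/200 = 12.0 days per admission; 2,400/2,500 = 0.960 days per patient.
- After averting 20 short stays: 2,340 bed-days; 2,340/180 = 13.0 days per admission (+8.3%); 2,340/2,500 = 0.936 days per patient (−2.5%).

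The total with zeros moves with bed-days.

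**ANCOVA.** If both the dependent variable and the covariate are per-admission LOS, a patient has both values only if admitted in both years. To show the order of magnitude only, assume 4% to 15% are admitted in a year.

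- Admission independent between years: from 2,500×0.04² = 4 to 2,500×0.15² ≈ 56 patients per group.
- 30% of those admitted in one year also admitted in the other: from 2,500×0.04×0.3 = 30 to 2,500×0.15×0.3 ≈ 112 patients per group.

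**The case against.** The strongest reply is that the article does not fix an analysis restricted to admitted patients. The governing phrase speaks of duration of utilization for the same patients over a year, and the per-admission words sit in a parenthetical list. They could describe the data item extracted, from which a yearly total is built. The research question's calendar days could also be a total. The LOS definition stands in the Background as a general quality indicator. Table S2, which details the variables, is not shown. The economic section says it reports the relevant primary and secondary outcomes in natural units and then names inpatient days, so that may be the intended duration outcome.

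Much of this stands. A reader might infer that the plan excludes patients without an admission, or codes them as missing. The text says neither, and both this and the ANCOVA restriction follow only from the per-admission reading. But that is the reading the words give in both places where LOS is specified, and nothing in the article states the alternative. If a total was meant, the outcome wording needs the same correction.

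A reader might also infer that the study would report harm from RASP. The article does not support that: admissions and costs are primary too, inpatient days are compared in the economic analysis, and the 10% hypothesis concerns utilization and cost without naming mean LOS. Nor do the documents show which stays RASP would avert, so a rise in mean LOS is possible but not predicted. Extending the point to readmissions would need a denominator that the article does not state.

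**Conclusion.** The point holds as a fault in how a primary outcome is defined. As worded, LOS per admission conditions on an event that RASP aims to reduce, and it differs from the inpatient-days measure in the economic evaluation. Its direction depends on which stays are averted: in the illustration, 15.0 to 17.5 days while bed-days go from 1,500 to 1,400, and the reverse movement in the mean if long stays are averted. The sign rule is arithmetic; the sizes rest wholly on assumed stay lengths and shares averted. On the same reading the ANCOVA would rest on patients admitted in both years, an unknown number that the expected 2,500 per group does not describe. The harm is limited to a misleading or contradictory LOS component. It should be corrected before the data are analysed, but it does not by itself invalidate the evaluation's overall result.

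**What to change.** Define the primary inpatient-duration outcome as total mental-health inpatient days per patient in the one-year window, with 0 for patients not admitted. Use this one measure in the research question on utilization, in Outcome measures, as both dependent variable and covariate in the ANCOVA, and as the inpatient days of the Health economic evaluation. Report LOS per admission descriptively only, beside the number of admissions.

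The cost is one definition carried through four places. It uses the same admission and discharge dates, needs no further extraction, and keeps every patient in the comparison. The total will contain many zeros and a long upper tail, so intervals for its mean difference should not lean on normality; the bootstrap already planned for the economic analysis could serve here as well.

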## Methods

### Study objectives

The primary objective of this study is to evaluate the effectiveness and impact of RASP on high-cost health services utilization (e.g. ED visits, mobile crisis visits and inpatient mental health utilization). To achieve this objective, we will conduct a within-subject comparison by analyzing health services utilization data from patients attending the RASP program one year pre- and post-assessment. Additionally, a between-subject comparison will be made using historical data from a control population consisting of patients referred by a PHP to see a mental health clinician before RASP implementation. Another primary objective is to assess qualitative data from healthcare partners' perceptions related to the impact of the RASP on access to community mental health care for patients and support for primary care providers, as well as to determine patient experiences and satisfaction with the program.

The secondary objectives of this study are to i) identify the sociodemographic characteristics of the population assisted by the RASP, ii) evaluate the prevalence and correlates of the various psychological conditions of the assisted population, iii) assess recovery, well-being, and risk measures in the assisted population at the program entry, and iv) compare health services utilization in the subset of patients who opt to participate in the Text4Support RCT with those who do not.

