### Participants and data collection

All RASP patients receive a consent form as part of their intake process, allowing access to their health services utilization records. Only those who sign the consent form will be part of the study. While consent is obtained during the initial assessment for ongoing patient recruitment, data collection is scheduled to commence after the program's first year, in April 2024. Service utilization data will extracted from provincial information systems retrospectively and prospectively at 2-time points: one year pre- and one-year post-assessment date at RASP. In addition, sociodemographic and mental health assessment information, including results from patient-completed validated scales and psychiatry diagnosis, and patient satisfaction will be extracted from routine paper-based initial screening forms. Patient satisfaction quantitative data will be extracted from RASP's patient satisfaction survey, available in a paper-based format and completed immediately after the assessment or REDCap online survey link sent via text message to all patients attending the service just after the assessment appointment.

The control group for the cohort study will comprise patients referred to the MHAP Central Intake Services by a PHP before RASP implementation. The periods for inclusion in the control group will be May 2017 to May 2019 (pre-COVID) and May 2020 to May 2022 (during COVID). By examining the data from these two time points (pre-COVID and during COVID) and comparing them with each other and with data during the RASP implementation period, we will be able to evaluate the impact of the pandemic on health services utilization as well as the impact of RASP implementation in comparison with both the pre-pandemic and during the pandemic periods. Ethics approval for exemption from requiring informed consent for all control group patients has been granted by the Research Ethics Board at Nova Scotia Health (REB file #1028254), allowing control group patients' sociodemographic and health services utilization information from provincial administrative databases to be accessed by the investigators.

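### The primary within-subject comparison uses raw yearly counts with no time at risk, so post-years cut short by death or leaving the province modestly favour the 10% reduction

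*Protocol article*

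**What the plan says.** Under Outcome measures, the primary outcome is the "mean differences in the frequency/duration/related costs of high-cost mental health services utilization", taken "between one year pre- and post-assessment date for same patients at RASP (within-subject comparison" and also between RASP patients and historical controls. The data are "extracted from provincial information systems retrospectively and prospectively at 2-time points" (Participants and data collection).

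The Quantitative analysis section names chi-square and t-tests for the pre-post comparison, and ANCOVA of post-year use on pre-year use for the comparison with controls. As described, none of these uses time at risk. The same section plans a sensitivity analysis around imputing lost data, without saying what counts as lost.

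The Hypothesis section states that "RASP will result in a minimum 10% reduction in high-cost health services utilization" and adds: "This forecast is expected to be found in both within-subject and between-subject comparisons".

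The Background remarks that "Patients with mental disorders have high mortality rates [22". A secondary objective is to "assess recovery, well-being, and risk measures in the assisted population at the program entry", and the listed scales include a suicide-risk scale. Death is not among the listed outcomes. The article states no rule for a patient who dies or leaves the province during the post-year.

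**The concern.** The two windows are not symmetric. A patient enters by attending the assessment, so the whole pre-year was survived by design. The post-year carries no such guarantee. In a utilization extract, the months after a death or a move away contain no visits, which looks the same as months in which a patient needed no care.

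With a raw yearly count as the outcome, these truncated post-years pull the post-year mean down, in the direction of the hypothesis. Related costs are part of the same outcome and inherit the problem. A fall in emergency and inpatient use is also hard to interpret in a psychiatric population if deaths over the same year are not shown beside it.

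**Working it through.** The plan gives no figure on this point to reproduce: it states no death rate, migration rate or loss to follow-up. Only a range under stated assumptions can be shown.

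**Inputs from the article:** one-year windows and mean differences (Outcome measures); provincial records (Participants and data collection); a target of at least 10% (Hypothesis).

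**Assumptions:** a share *d* of patients die in the post-year, spread evenly, so each loses half a year on average. Their rate of use is *k* times the cohort mean in both years. There is no true effect.

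**Step 1: spurious fall.** Set the pre-year mean to 1. The post-year mean is 1 − 0.5·d·k, so the apparent fall is 0.5·d·k.

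| Deaths *d* | k = 1 | k = 3 | k = 5 |
|---|---|---|---|
| 1% | 0.5% | 1.5% | 2.5% |
| 2% | 1.0% | 3.0% | 5.0% |

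If relative use *r* is instead defined against the survivors, the fall is 0.5·d·r/(1 − d + d·r). For (1%, 1) this is 0.5%; for (1%, 5) it is 0.025/1.04 = 2.4%; for (2%, 5) it is 0.05/1.08 = 4.6%. The definition hardly matters.

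**Step 2: what would produce the whole 10%.** Solving 0.5·d·k = 0.10 gives d = 20% (k = 1), 6.7% (k = 3) and 4% (k = 5). All lie above the 1% to 2% assumed here.

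**Step 3: can it reverse?** Suppose the 1% who die had average pre-year use but five times the average rate from assessment until death. The post-year mean is then 0.99 + 0.01 × 0.5 × 5 = 1.015, an apparent rise of 1.5%. The direction in Step 1 therefore depends on those who die having similar rates of use in both years.

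**Step 4: migration.** If 3% leave during the post-year with average use, post-year recorded use falls by 0.03 × 0.5 = 1.5%. If 3% arrived during the pre-year, pre-year recorded use is low by the same 1.5%. The ratio is 0.985/0.985 = 1. Equal flows cancel; only the imbalance matters.

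**Step 5: between groups.** With no true effect, equal loss and equal *k* lower both group means alike and create no difference. With 2% loss in RASP and 1% in controls, the spurious difference is 0.5 × (0.02 − 0.01) × k, which is 0.5% at k = 1 and 2.5% at k = 5. Loss in the other direction reverses the sign.

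**The case against.** The strongest reply is that this is silence, not a rule. The article is condensed, the supplementary table of variables (Table S2) is not shown, and censoring is often left to an analysis plan. This stands in part: nobody can say from the article that vital status will not be extracted. But the article does fix the outcome as a mean difference in yearly amounts and names tests that take no exposure time, so having the dates would not by itself correct the analysis.

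A second reply is the planned sensitivity analysis on imputed data. It is undefined, and it does not clearly reach this problem: absence of visits after death does not register as missing, and imputing visits after death would be wrong.

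Third, the Background sentence on mortality concerns people with mental disorders in general. It gives no rate and is not about RASP attendees, so it is a reason to look and no basis for a number. This stands.

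Three stronger readings may tempt a reader, and the documents support none of them:

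- *Each patient who dies is scored as a success.* Step 3 shows otherwise, and a patient with no pre-year use cannot show a fall. The bias lies in the mean.
- *Truncation explains more than half of the 10% target.* This requires adding 1.5% for departures to the highest mortality case (4.6% + 1.5% = 6.1%) while ignoring newcomers, who act in the opposite direction.
- *A reduction should not count as benefit if RASP deaths are higher.* With the 2500 per group in Sample size considerations and an assumed 1% mortality, about 25 deaths are expected in each group. If true mortality is equal, the chance of a tie is about 1/(2√(π × 25)) = 0.056, so RASP deaths exceed control deaths by chance about (1 − 0.056)/2 = 47% of the time. The controls are also historical and partly from the COVID period.

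**Conclusion.** The point holds for the primary within-subject comparison. Raw counts over nominal years, in patients who all survived the first year and may not all survive or stay for the second, tend to understate post-year use and so modestly favour the hypothesised reduction.

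Under assumed deaths of 1% to 2% a year, at mid-year on average, and use of 1 to 5 times the mean in both years, the spurious fall is about 0.5% to 5%. That is a part of the 10% target. It could be smaller, or reversed, if use climbs before death. The net effect of migration has no known sign. In the comparison with controls there is bias only if loss differs, and the documents give no evidence on that.

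The change should be made because it is cheap, and because dates left out of the extraction cannot be supplied by a later analysis plan.

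**What to change.** 1. Include date of death and, where available, start and end of provincial coverage in the planned extraction, for RASP and control patients alike. Confirm in Table S2 and in the ethics approval that these are covered: as described in Participants and data collection, RASP consent refers to utilization records and the control waiver to sociodemographic and utilization information, and neither names vital status.
2. Analyse each outcome per person-year alive and covered, in the pre-year as well as the post-year, for example with a count model and a log person-time offset. Applying this to the pre-year also deals with newcomers whose earlier use was not captured.
3. Report one-year all-cause deaths in RASP and control patients descriptively beside the utilization result, with a confidence interval for the difference and without a veto rule.

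The cost is one or two extra variables, possibly a short ethics amendment, and probably a slightly less favourable reduction.
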